#### Exclusion criteria

We exclude women who show complications during the study, have preterm labor, and are reluctant to continue to participate in this study.

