### Eligibility criteria {10}

#### Inclusion criteria

The criteria for entering women are being literate, being in gestational age 24 to 32 weeks, being able to speak Persian, having no complications in the current pregnancy, having no indications for CS, and having enough time to participate in the interventions.

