### Criteria for discontinuing or modifying allocated interventions {11b}

The intervention will be discontinued based on the participant’s request, or if a woman undergoes birth.

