## Assignment of interventions: allocation

### Sequence generation {16a}

The participants will be randomly assigned to four groups after the initial assessment and upon completing the baseline data form. We will recruit the participants based on the registration order of women with the clinic, and no other factor will contribute to participants’ order on the list. Each participant on the list will be assigned a consecutive research identification number according to the order by which they will be registered with the clinic. The first participant on the list will be randomly assigned to the MI intervention group, and the next two participants will be assigned to the IMB and IMB-App interventions, respectively. The fourth participant will be assigned to the control group.

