### Data management {19}

To ensure that the data is correctly entered, a double entry of data will be performed by two different individuals. Pregnant women who refer to the hospital will be registered, by chronological order of selection, and they will be allocated randomly in each group. All data obtained from women will be entered to SPSS software. A code will be defined to identify missing data. After screening the data and preparing the data for statistical analysis, first using descriptive statistics such as frequency tables, means and standard deviation, and bar chart and histogram, the distribution of variables will be checked. The obtained data will be kept strictly confidential and will be stored with secured and restricted access; also, the signed consent will be kept locked. Follow-up data are received using the same questionnaires as used at baseline.

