### Methods in analysis to handle protocol non-adherence and any statistical methods to handle missing data {20c}

This is not applicable.

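### Women are excluded after allocation for complications, preterm labour or reluctance, and no stated rule keeps them in the primary comparison of mode of delivery

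*Protocol article*

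**What the plan says.** The Exclusion criteria section of the Protocol article is one sentence: "We exclude women who show complications during the study, have preterm labor, and are reluctant to continue to participate in this study". I read it as meaning any one of the three conditions. The Inclusion criteria require, among other things, "having no complications in the current pregnancy, having no indications for CS, and having enough time to participate in the interventions". Sequence generation {16a} fixes the time of allocation: "The participants will be randomly assigned to four groups after the initial assessment and upon completing the baseline data form". The primary outcome, mode of delivery, is recorded after childbirth ({18a}).

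Several sections touch on women who stop:

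- Criteria for discontinuing {11b}: "The intervention will be discontinued based on the participant’s request, or if a woman undergoes birth".
- Section {20c}, headed "Methods in analysis to handle protocol non-adherence and any statistical methods to handle missing data", is answered only by saying that the item does not apply.
- Data management {19}: "A code will be defined to identify missing data". No analysis rule goes with it.
- Section {18b} promises follow-up to delivery, without saying whether this covers women who have been excluded.
- Statistical methods {20a} lists tests and a logistic regression, and names no set of women to be analysed.

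**The concern.** Exclusion criteria normally describe the woman before she is allocated. These describe what happens to her afterwards. Complications and preterm labour can each lead to a cesarean, so the rule selects on events related to the primary outcome. Reluctance may depend on the arm: three arms ask for counselling sessions or app use, the control arm asks for neither, and {17a} says that participants and researchers cannot be blinded. Complications are not defined in the exclusion rule, and the article does not say who judges them or whether that person knows the arm.

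If such women leave the analysis, the groups compared are no longer the groups allocated, and a difference between them can partly reflect who was removed. Two sections also disagree. Under {11b} a woman's request ends the intervention, whereas under the Exclusion criteria her reluctance ends her place in the study.

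**Working it through.** **Inputs from the document.** 30 women per arm, 120 in total, 80% power ({14}); significance level 0.05 ({20a}), taken as two-sided; cesarean rate in Iranian private hospitals 72–89% (Background {6a}). **Assumed, because the document gives no figure:** every exclusion rate, the planned cesarean rates by arm, and the delivery mode of excluded women.

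**1. The plan's own figure.** 4 × 30 = 120, which agrees. The 80% power cannot be reproduced because the minimum difference is not given.

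**2. Timing.** A woman with a complication at screening already fails the Inclusion criteria. A complication arising during the study, preterm labour, or reluctance to go on can therefore only come after enrolment. Allocation follows at once on the baseline form, so these are exclusions after allocation.

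**3. Complications, if they arise in attempted vaginal births.** Assume planned cesarean in 80% of controls and 60% of an active arm, and that 20% of attempted vaginal births become cesarean for complications.
- All allocated: control 0.80 + 0.20 × 0.20 = 0.84; active 0.60 + 0.40 × 0.20 = 0.68; difference 16 points.
- Those women excluded: control 0.80 / (1 − 0.04) = 0.833; active 0.60 / (1 − 0.08) = 0.652; difference 18.1 points.
- Ratio 18.1 / 16 = 1.13, an overstatement of about 13%.
- With no effect on planned mode, both arms change equally and no difference appears.

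**4. Reluctance, with no true effect.** Let both arms have 24/30 = 80% cesarean. Remove from one arm 6 women who would all deliver by cesarean: (24 − 6)/(30 − 6) = 18/24 = 75%, a spurious 5 points. In general, the retained rate = (R − wq)/(1 − w), where R is the full rate, w the excluded share and q the cesarean rate among the excluded. With R = 0.72 and exclusion in one arm only:
- w = 0.10, q = 0.90: 0.63/0.90 = 0.70, a spurious 2 points.
- w = 0.20, q = 1.00: 0.52/0.80 = 0.65, a spurious 7 points.
- w = 0.30, q = 1.00: 0.42/0.70 = 0.60, a spurious 12 points.

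**5. Exclusions unrelated to arm.** Power = Φ{[√n × d − 1.96 × √(2p̄(1 − p̄))] / √(p₁(1 − p₁) + p₂(1 − p₂))}. With a 72% control rate and 30 per arm, 80% power corresponds to 72% vs 36.6%, so d = 0.354 and p̄ = 0.543.
- n = 30: (1.939 − 1.381)/0.658 = 0.85, power 0.80.
- n = 24 (20% excluded): (1.734 − 1.381)/0.658 = 0.54, power 0.70.

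**6. Outcome unknown.** If 6 of 30 in each of two arms have no recorded delivery mode, the bounds on the risk difference span 6/30 + 6/30 = 40 points. That is wider than the 35-point difference in step 5.

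**The case against.** The other side has several fair points.

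- **The article does not say that excluded women leave the analysis, or that their deliveries go unrecorded.** Section {11b} can be read as ending only the intervention, and {18b} follows participants to delivery. This stands as a limit. But with an exclusion rule, no named analysis population and {20c} set aside, removal is the natural reading.
- **Not-applicable entries look like template filler.** Section {11c} uses one for adherence strategies although the app description includes reminders. Detailed missing-data methods also often belong in an analysis plan. Both are true, but {20c} is a positive statement that conflicts with an exclusion rule foreseeing withdrawals.
- **The complications meant may be antenatal.** If they are unrelated to counselling, excluding them changes the population and costs power without favouring an arm. This stands, and step 3 depends on the other meaning.

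Three stronger readings are tempting and are not supported. A reader might infer that women are selected on the outcome itself; the rule selects on events related to delivery mode, not on delivery mode. A reader might infer that only the active arms can lose women; controls also answer the follow-up questionnaire ({18a}, {19}), are followed to delivery and can withdraw, and nothing shows that those who leave prefer cesarean. Finally, if 20% have complications in both arms whatever the planned mode, excluding them all gives 80% vs 60%, or 20 points instead of 16. That might be called a 25% bias, but it is the effect in women without complications, which is a different target. Given the trial's interest in unnecessary cesareans, that target is arguable.

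**Conclusion.** The point holds in this form: the article states exclusions that occur after allocation and relate to the primary outcome, sets aside methods for non-adherence and missing data, and gives no rule that restores a comparison of all allocated women. The Exclusion criteria and {11b} also need to be reconciled.

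The direction and size of any bias are not established. Unequal burden and an unblinded design make withdrawal that differs by arm plausible, no more. On the assumed figures, the distortion is about 2 points from intrapartum complications when there is a true effect, and 5 points from one-sided loss of 6 in 30 when there is none. The 12-point case needs 30% one-sided exclusion with every excluded woman delivering by cesarean. If exclusions do not depend on arm, the cost is power (about 0.80 to 0.70 at 20% exclusion) and a narrower population. The point should be corrected before analysis, because delivery mode that is not collected may be hard to recover later.

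**What to change.** 1. Limit the Exclusion criteria to conditions present before allocation.
2. State that the primary analysis includes all allocated women in their allocated arm.
3. Reconcile the Exclusion criteria with {11b}, stating that stopping the sessions or the app is not leaving the study.
4. Record mode of delivery for every woman, including those with complications or preterm labour, unless she withdraws consent for use of her data.
5. Replace the entry in {20c} with this rule, plus a best/worst-case sensitivity analysis for unknown deliveries.
6. Show the subset without complications or preterm labour as a secondary analysis only.

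The cost is a change of wording, some retrieval of delivery mode for women who stop, and an effect estimate that may be less favourable. Recruiting extra women would restore power but would not remove the selection.

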### Who will take informed consent? {26a}

Written informed consent will be obtained from all the participants by the principal investigator or sub-investigators prior to enrollment.

### Additional consent provisions for collection and use of participant data and biological specimens {26b}

This is not applicable. No biological specimens will be collected for research purposes; hence, no additional consent will be sought from the participants.

## Interventions

### Explanation for the choice of comparators {6b}

This is not applicable.

### Intervention description {11a}

The content of interventions will be designed based on a qualitative evidence synthesis and a quantitative systematic review and meta-analysis in Iran [55]. Also, we will design the interventions tailored to the participants’ needs. The interventions are expected to take around 2 months to be completed, and women will be followed up until their delivery time.Motivational interviewing (MI)In this intervention group, pregnant women will be trained face-to-face based on the MI. During three 45–60-min sessions, MI techniques will be provided to the participants. MI is a directive, client-centered counseling style for eliciting behavior change by helping clients to explore and resolve ambivalence. It is most centrally defined not by technique but by its spirit as a facilitative style for interpersonal relationships. MI is a relatively simple, transparent, and supportive talk therapy based on the principles of cognitive-behavior therapy. In this group, we will help women to explore and resolve ambivalence about the mode of delivery and build their intrinsic motivation.We will not force women to choose a specific mode of delivery. We will ask open-ended questions (for example, “Tell me what you think about CS?” or “What do encourage you to choose this type of delivery (CS or NVD)?”). Open-ended questions can help us to understand how they are thinking about the mode of delivery. Affirming is one of the fundamental MI skills. We will use it to support engagement, encourage the women to further explore change processes, and build confidence. We will find an opinion the client is making or a strength she will notice and reflect it to her (for example, “So how did you manage to control your fear after attending our training sessions?”). We will use reflective listening as a simple method to reduce resistance in MI. The last step of this technique is to summarize what the pregnant women have said.Information, motivation, and behavioral skills model through a face-to-face approach (IMB)During three 45–60-min sessions, the model’s strategies will be provided to the participants. Participants will receive information and behavioral skills related to the choice of mode of delivery as well as internal and external motivational factors related to the choice of delivery. The strategy includes the following: (1) *Information*—the intervention will begin with information on the prevalence of CS and CS-related complications in women, and outcome of unnecessary CS; (2) *Motivation*—the interventionist will perform this technique to motivate pregnant women, providing personal feedback, asking open-ended questions, affirming desirable behavior, reflective listening, working at the women’s pace, and negotiating goals that will be realistic and attainable; and (3) *Behavioral skills*—women will be given behavioral skills training on how to control the obstacle of NVD. To build skills for choosing the mode of delivery, training will be given on how to reduce these barriers.Information, motivation, and behavioral skills model through mobile app (IMB-App)The mobile application (M-health) has been designed based on the IMB model. The software will be installed on mobile phones of participants in the group, and its operation will be taught individually. Women will work with the application in the presence of the research team, and any existing problems will be resolved. The strategies foreseen for adherence improvement include reminders set at defined intervals in the form of pop-up messages. To monitor adherence, the data collected on the server will be used. In addition to the application, a server will be designed in which the users’ activities will be collected. Items such as the duration of application usage and the sections used by the user (in addition to registering their time and duration) will be registered. Every time the user’s mobile is connected to the Internet, the data will be uploaded and saved on to the server. These data can be used as a proxy of adherence to the intervention.

*Control group*: without any intervention

### Criteria for discontinuing or modifying allocated interventions {11b}

The intervention will be discontinued based on the participant’s request, or if a woman undergoes birth.

### Strategies to improve adherence to interventions {11c}

This is not applicable.

### Relevant concomitant care permitted or prohibited during the trial {11d}

Usual prenatal care will be provided in all study groups.

### Provisions for post-trial care {30}

This is not applicable.

### Outcomes {12}

Determining and comparing the effects of MI, IMB, and IMB-App on mode of delivery in the target and control groups before and after the interventions.Determining and comparing the effects of MI, IMB, and IMB-App on the intention of performing CS in women in the target and control groups before and after the interventions.Determining and comparing the effect of MI, IMB, and IMB-App on women’s self-efficacy in target and control groups before and after the interventions.

### Participant timeline {13}

The recruitment of participants for this study started in December 2019 and is still ongoing. The recruitment is expected to be completed in April 2020; the data analysis, writing of scientific manuscripts, and submissions to peer-reviewed scientific journals will occur from 2020 to 2021.

### Sample size {14}

The sample size is 120 pregnant women (30 in each group) with a power of 80% to detect a minimum difference.

### Recruitment {15}

We will be present in the research setting during the intervention period to recruit all eligible women. The study will be available to all pregnant women interested in participating and speaking Persian. Individuals who fulfill the inclusion criteria will receive a description of the study, indicating the follow-up schedule and assurance of confidentiality, and they will be directed to complete a consent form. Included participants will be randomly allocated in three intervention groups and one control group.

## Assignment of interventions: allocation

### Sequence generation {16a}

The participants will be randomly assigned to four groups after the initial assessment and upon completing the baseline data form. We will recruit the participants based on the registration order of women with the clinic, and no other factor will contribute to participants’ order on the list. Each participant on the list will be assigned a consecutive research identification number according to the order by which they will be registered with the clinic. The first participant on the list will be randomly assigned to the MI intervention group, and the next two participants will be assigned to the IMB and IMB-App interventions, respectively. The fourth participant will be assigned to the control group.

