### Concealment mechanism {16b}

Randomization will be performed by a person who will not be engaged in the study and will be blinded to the identity of the participants.

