## Assignment of interventions: blinding

This is not applicable. It is not possible to mask this study because of its nature. To avoid bias in the outcome assessment, research assistants concerned with data collection and/or preparation will be blinded to the allocation of the participants.

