### Who will be blinded {17a}

As the RCT is an educational intervention study, blinding of participants and researchers is not possible. To minimize selection bias, we will use randomization.

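### The sequence-generation rule, as written, is a fixed order by clinic registration; this contradicts the random allocation claimed elsewhere and leaves nothing to conceal

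*Protocol article*

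**What the plan says.** In the protocol article, Sequence generation {16a} opens by saying that women are randomly assigned after the initial assessment and baseline form. It then sets out the mechanism:

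- Order of the list: "We will recruit the participants based on the registration order of women with the clinic", with no other factor affecting that order.
- Study ID: each woman receives a "consecutive research identification number according to the order by which they will be registered with the clinic".
- Position 1: "The first participant on the list will be randomly assigned to the MI intervention group".
- Positions 2 to 4: "the next two participants will be assigned to the IMB and IMB-App interventions, respectively. The fourth participant will be assigned to the control group".

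Other sections rely on the allocation being random:

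- Concealment mechanism {16b}: "Randomization will be performed by a person who will not be engaged in the study". That person is also said to be unaware of participants' identity.
- Who will be blinded {17a}: "To minimize selection bias, we will use randomization".
- The blinding section: "research assistants concerned with data collection and/or preparation will be blinded to the allocation of the participants".
- Recruitment {15} and Data management {19} also call the allocation random.

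**The concern.** An arm that is named in advance for a given list position is not the result of a random draw. The {16a} sentence that assigns the first woman at random to a named arm contradicts itself. The next two sentences fix the remaining three arms in the same way.

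The trial does not mask participants or researchers, and {17a} offers randomization as the protection against selection bias. The study team recruits on site (Recruitment {15}). One inclusion criterion, whether a woman has time for the intervention, is a matter of judgement. A recruiter who can see that the next position is control, or an active arm, can enrol or pass over a woman according to how set she seems on cesarean section, even without intending to. The article itself gives women's preference as a main driver of cesarean section, so such selection would bear directly on the primary outcome.

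**Working it through.** **1. Does the rule fit the planned sample size?** Sample size {14} gives 120 women, 30 per group. Repeating MI, IMB, IMB-App, control over IDs 1 to 120 gives 120/4 = 30 per arm, which matches. The arm is then a function of the ID: remainder 1 on division by 4 is MI, 2 is IMB, 3 is IMB-App and 0 is control. The match supports the repeating reading but does not prove it, because {16a} gives only four positions.

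**2. How predictable is the next assignment?** Expected share that a recruiter who knows the scheme can guess correctly:

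| Scheme | Calculation | Share |
|---|---|---|
| Order in {16a}, repeated | 120/120 | 100% |
| Same order, random starting arm | (119 + 0.25)/120 | 99.4% |
| Random permuted blocks of 4, size known | (1/4 + 1/3 + 1/2 + 1)/4 | 52.1% |
| Simple randomization | 1/4 | 25% |

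A random starting arm, which is one generous way to read the word random in {16a}, changes almost nothing. The fair comparator for a four-arm trial that wants equal groups is the permuted-block row. Blocks of randomly varying size would be less guessable than 52.1%, though still above 25%.

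**3. Can {16b} conceal the allocation?** Concealment needs a sequence that recruiters cannot foresee. Under {16a} the registration list fixes the arm, and that list exists before the independent person acts. Using an outside operator who does not know the women's identity hides nothing from someone on site who sees the list.

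**4. How large could the bias be?** The documents give no figure for steered enrolment, so this is an illustration. Suppose 3 women certain to have a cesarean fill control positions instead of positions in one active arm of 30, in exchange for 3 others.

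- Ceiling: the 3 exchanged women would all deliver vaginally. Each arm moves by 3/30 = 10 points, so the difference moves by 20 points.
- If the exchanged women have average rate p, the difference moves by 2 × 3 × (1 − p)/30. Taking p from the private-hospital range in the Background (72–89%), this is 2 × 3 × 0.28/30 = 5.6 points at 72% and 2 × 3 × 0.11/30 = 2.2 points at 89%.

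For scale, with 30 per arm, two-sided 0.05 and 80% power, the detectable fall in the cesarean rate is about 35 points from 72% and 31 points from 89%. The control rates and the two-sided test are assumptions here; {14} states no target difference.

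**5. Blinding of data collectors.** IDs run in the same order as the allocation. A data collector who sees the ID and knows the rule can therefore work out the arm.

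**The case against.** The strongest reply is that {16a} may be a clumsy worked example. It uses the word random, {16b} has an uninvolved person perform randomization, and the order could be redrawn within each set of four. The text does not exclude this. It is the less natural reading, because {16a} fixes the first four positions and mentions no redraw. Even if it is true, {16a} misdescribes the method and needs correcting.

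There are also partial safeguards. The team intends to recruit all eligible women, nothing but registration sets the list order, and assignment follows baseline. These narrow a recruiter's discretion. They do not remove it while the next arm is foreseeable at screening and consent.

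A reader might infer more than the documents support:

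- *That the protocol states a repeating rotation, so every assignment is known as a matter of fact.* The repetition is an inference, and the 100% depends on it.
- *That the cost is the gap between 100% and 25%.* The 25% belongs to simple randomization. The practical alternative is permuted blocks, at about 52% for known blocks of four.
- *That a 20-point bias should be expected.* That is a ceiling, and it needs women certain to have a cesarean exchanged for women certain to deliver vaginally. The average-rate version gives 2.2 to 5.6 points, and the count of three women is itself an assumption.
- *That data-collector blinding fails outright.* It is undermined only if collectors see the ID and know the rule, and the article states neither. Mode of delivery, taken from a checklist after birth, is little exposed to this. The self-reported secondary outcomes are more exposed, although those women are unblinded anyway.
- *That selection bias has occurred.* The text shows vulnerability only.

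**Conclusion.** The point stands as a fault in the allocation as described. {16a} sets out systematic allocation by registration order with no random source, and this cannot be squared with {15}, {16b}, {17a} and {19}. If the order repeats, all 120 assignments are foreseeable, the concealment in {16b} has nothing to protect, and selection bias can enter the primary comparison. The effect on the estimate cannot be fixed from the documents. Under the assumed three-woman exchange it runs from about 2 points to a ceiling of 20. The threat to data-collector blinding is secondary and conditional. The matter must be resolved before the trial is reported as randomized, because {17a} offers no other protection against selection bias and the tests listed in Statistical methods {20a} cannot restore it afterwards.

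**What to change.** First, establish and document how women have actually been allocated. Then:

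- **If a proper random list was used**, correct {16a} to describe how it was generated and released.
- **If the rotation was used**, replace it for all women not yet allocated with a computer-generated 1:1:1:1 permuted-block list with randomly varying block sizes, for example 4 and 8. The uninvolved person in {16b} should generate and hold it, and release each assignment only after consent, eligibility and baseline are recorded. The post-baseline timing is already in {16a}. Make study IDs independent of allocation.
- **For women already allocated by rotation**, flag them, report that part as quasi-randomized, and run a sensitivity analysis without them where enough women remain.

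The cost is a protocol amendment, one list, and sealed envelopes or a telephone or web release; the planned number of women does not change. Timing is the real limit. Recruitment began in December 2019 and was due to end in March 2020 (Trial status) or April 2020 (Participant timeline {13}). If most women have already been allocated, the sensitivity analysis may have too few women to be informative with 30 per arm, and the randomized label must be qualified in the report.
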